### Study Arms

#### PHN

PHN is based on the theoretical foundation of social cognitive theory (SCT). Participant-centered PHN helps to (1) identify barriers to HIV care, (2) identify and link participants to needed auxiliary services, and (3) increase participants’ self-efficacy in working with HIV care providers and other social service and treatment facilities. PHNs do not provide counseling or psychotherapy; they work with each participant to successfully navigate complicated health care and social service systems. The PHN intervention uses an individualized, participant-centered treatment plan with the goals of removing multiple and complex barriers that can impede linkage to and retention in HIV care and medication adherence to achieve virological suppression. Each participant works with a PHN to develop a participant-centered treatment plan and get linked to HIV care or other needed auxiliary physical, mental health, and psychosocial services (eg, hormone therapy, dental care, hepatitis testing or care, SUD treatment, mental health treatment, legal services, and job training or development; Figure 2). A priority of the first session is to schedule an HIV care appointment for the participant if needed. The PHN also works with each participant to establish HIV self-efficacy regarding her treatment plan. To establish an immediate connection, participants are introduced to a PHN immediately following randomization. PHN sessions are unlimited for 90 days.

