### Statistical Analyses

#### Aim 1

The primary outcome of HIV care will be viral suppression (defined as less than 200 copies/mL). Secondary outcomes include the HIV-ASES, the HIV Treatment Optimism Scale, the ISSB, and urine drug screen results (test results for each of the 5 substances identified in the urine drug screen will be treated as different indicators). These outcome variables will be assessed at baseline and 3, 6, 12, and 18 months post enrollment. The resulting dependent variables will fall into one of two categories: (1) dichotomous variables (primary outcome: virologic suppression, and secondary outcome: urine drug screen results), assumed to follow a binomial distribution; or (2) continuous random variables (secondary outcomes: HIV-ASES, HIV Treatment Optimism Scale, ISSB scores), assumed to follow a normal distribution. All distributional assumptions will be evaluated prior to the conduct of analyses, and statistical methods chosen accordingly. Each of these dependent variables will be separately regressed on treatment condition (PHN alone vs SMS text messaging alone vs PHN+SMS text messaging), a set of baseline covariates (individual-level demographic characteristics), and time-varying covariates (social and structural determinants of health), using hierarchical linear regression where responses at each time point are nested within individuals. All analyses will be conducted on available study-related data from all participants, regardless of whether or when they drop out of treatment. The effect of interest will be a time × treatment condition interaction effect which will estimate the differential course and impact of the three intervention modalities over the follow-up period.

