A generalized linear mixed model (GLMM) [54-56] will be used to conduct analyses of all outcomes following an intent-to-treat approach. The GLMM is an ideal statistical procedure for analyzing a broad class of longitudinal outcomes, including costs. As described above, key indicators of HIV care will be regressed on treatment conditions and a series of baseline and time-varying covariates. Treatment condition will be used to predict the slope of time, creating a time × treatment interaction term that is the effect of interest in the proposed study. We will also report on the relationships between time-varying covariates and the outcome measures, including time-shifted analyses where the value of the covariate at a previous timepoint is used to predict the outcome measure at a subsequent timepoint. Hypothesis testing for any given outcome will involve fitting the statistical model of interest and testing the effect of interest, as well as all other estimable effects in the model. We will use an iterative model-building approach where the simplest model is fit to the data first, and additional explanatory factors are added iteratively, in order of theoretical importance. Likelihood ratio tests are used to determine if the more complicated of the 2 models is a significant improvement over the simpler model. Variables of interest such as those specified in Aim 1 will always be included in the final model as the statistical tests of those parameter estimates (be they significant or nonsignificant) are of primary interest to this study.

#### Aims 2 and 3

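### The stated Aim 1 model has no navigator level, so intervals for the two PHN-containing arms against SMS may be too narrow if outcomes correlate within navigator

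*Protocol article*

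**What the plan says.** All references are to the Protocol article.

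- **Model (Statistical Analyses, Aim 1).** Each outcome is regressed on arm and covariates by "hierarchical linear regression where responses at each time point are nested within individuals". A generalized linear mixed model "will be used to conduct analyses of all outcomes following an intent-to-treat approach".
- **Effect of interest.** "Treatment condition will be used to predict the slope of time, creating a time × treatment interaction term".
- **Room for further terms.** In model building, "additional explanatory factors are added iteratively, in order of theoretical importance". Navigator is not named among them, either as a random effect, as a fixed effect or as a cluster for the variance.
- **PHN arm (Study Arms, PHN).** "Each participant works with a PHN to develop a participant-centered treatment plan", and "participants are introduced to a PHN immediately following randomization". Sessions are unlimited for 90 days. The plural in "PHNs do not provide counseling or psychotherapy" suggests more than one navigator, but no number or caseload is given.
- **Combined arm (Study Arms, PHN+SMS Text Messaging).** It receives the same navigation as the PHN arm, plus the messages.
- **SMS arm (Study Arms, SMS Text Messaging).** Messages come from an automated system with no navigator.
- **Power Analysis.** The sample size of 195, 65 per arm, rests on simulation. Clustering is not mentioned.

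**The concern.** Participants who share a navigator may have more similar outcomes than participants who do not. Navigation is individualized, open-ended over 90 days and meant to work through linkage to care and self-efficacy, so differences between navigators are plausible. The SMS-alone arm has no such source of correlation.

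A model whose only grouping level is the person treats the 65 participants of a PHN-containing arm as 65 independent units. If navigators differ, part of the difference between that arm and SMS reflects which navigators were employed, and the standard error omits that part. Baseline data cannot remove it: navigator contact starts after randomization, so a navigator effect appears as change from baseline, which is what the time × treatment term measures.

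The contrasts exposed are PHN vs SMS and PHN+SMS vs SMS. They bear on whether paying for navigators is justified, and the article says its findings are to guide service provision and policy. An interval that is too narrow there would overstate the evidence in either direction.

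**Working it through.** **The plan's own figure.** 3 × 65 = 195 checks. The power simulation cannot be re-run because the article does not print its inputs. That is normal for a condensed article and is not part of this point.

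**Inputs.** From the article: 65 per arm; navigators in two arms and none in the third. Assumed, because not given: k navigators serving an arm, with k from 2 to 6 and equal caseloads, and a navigator ICC of 0.02 to 0.05.

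**Formulas** for a PHN-containing arm vs SMS at a single time point:

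- cluster size m = 65/k
- design effect in the PHN-containing arm, DE = 1 + (m − 1) × ICC; in the SMS arm it is 1
- true-to-naive standard error ratio r = √((DE + 1)/2)
- actual two-sided error at nominal 5% = 2 × (1 − Φ(1.96/r))

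**Worked case,** k = 2 and ICC = 0.05: m = 32.5; DE = 1 + 31.5 × 0.05 = 2.575; r = √(3.575/2) = 1.337; 1.96/1.337 = 1.466; error = 14.3%.

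| k | ICC | DE | r | Error, formula | Simulation, binary | Simulation, continuous |
|---|---|---|---|---|---|---|
| 2 | 0.02 | 1.63 | 1.147 | 8.7% | 7.6% | 8.6% |
| 2 | 0.05 | 2.58 | 1.337 | 14.3% | 12.3% | 13.7% |
| 3 | 0.02 | 1.41 | 1.098 | 7.4% | 6.6% | 7.5% |
| 3 | 0.05 | 2.03 | 1.232 | 11.2% | 9.3% | 11.0% |
| 4 | 0.02 | 1.30 | 1.074 | 6.8% | 5.8% | 6.7% |
| 4 | 0.05 | 1.76 | 1.175 | 9.5% | 7.9% | 9.7% |
| 6 | 0.02 | 1.20 | 1.048 | 6.1% | 5.3% | 6.1% |
| 6 | 0.05 | 1.49 | 1.116 | 7.9% | 6.7% | 7.6% |

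The binary simulation used 20,000 trials, a response rate of 0.5, a navigator effect on the logit scale and a two-proportion z test. That test rejected 4.6% of the time with no navigator effect. The continuous simulation used 10,000 trials per cell and a two-sample t test. At ICC = 0 the formula returns exactly 5%.

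**PHN vs PHN+SMS.** If the same navigators serve both arms, a common navigator effect cancels. The ratio is then √(1 − ICC), which is 0.990 at ICC 0.02 and 0.975 at 0.05, and the simulated error is about 4.5%. With separate navigators for each arm it would not cancel. The article does not say which applies.

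**How far this carries to the planned slope test.** Take visits at 0, 3, 6, 12 and 18 months: mean 7.8, sum of squared deviations S = 208.8. Assume a linear approximation, total variance 1 and within-person residual variance 0.5. The naive variance of one arm's slope is 0.5/(65 × 208.8) = 3.68 × 10⁻⁵. A navigator effect with time profile f(t) adds (ICC/k) × (Σ(t − 7.8)f(t)/S)². With k = 2 and ICC = 0.05:

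- constant step after baseline: Σ = 7.8; added 3.49 × 10⁻⁵; r = √(1 + 3.49/7.37) = 1.214; error about 11%
- full at 3 months, fading linearly to zero at 18 (f = 0, 1, 0.8, 0.4, 0): Σ = −4.56; added 1.19 × 10⁻⁵; r = 1.078; error about 7%
- growing in proportion to time (f = t/18): Σ = 11.6; added 7.72 × 10⁻⁵; r = 1.431; error about 17%

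With k = 6, ICC = 0.02 and the fading profile, the error is about 5.3%. The slope test can therefore be affected less or more than the single-time comparison, depending on how a navigator effect evolves after the 90 days.

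**The case against.** Four objections have weight.

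1. *The article is condensed.* The sentence on nesting explains how repeated measures are handled. It does not exclude another level, and the model-building paragraph allows terms to be added. A reader might infer that the trial has decided to ignore navigators. The article does not show that: a navigator term could sit in the full protocol or analysis plan. What remains is that the article chose to state the hierarchy, gave one level, and described a delivery structure that this level does not match.

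2. *No ICC is given.* A reader might also infer that the standard errors are too small, or that there is a small set of navigators. Neither is in the document. With a zero ICC nothing is understated. This stands, and the point is conditional for that reason.

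3. *It depends on the target of inference.* If conclusions concern only the navigators in this trial, variation between them is not sampling error and the person-level standard error is not understated by it. This also stands. The aim of guiding services and policy, however, points to a wider target.

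4. *Few navigators cannot support a variance estimate.* True with 2 to 4. With a single navigator, the navigator cannot be separated from the intervention at all. But fewer navigators also mean larger clusters, so the difficulty of estimation is no sign that the problem is small. It argues for a sensitivity analysis and against changing the primary model.

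**Conclusion.** The point holds in conditional form. As stated, the Aim 1 model has one grouping level in a partially nested design. If outcomes correlate within navigator, and if conclusions are meant to extend beyond these navigators, standard errors for PHN vs SMS and PHN+SMS vs SMS are understated. PHN vs PHN+SMS is largely unaffected when navigators are shared.

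The size cannot be fixed from the document. Over the assumed ranges the true standard error of a single-time comparison is about 5% to 34% larger than the naive one (r from 1.048 to 1.337). The 6% to 14% error range should not be read as the error rate of the planned analysis: it is for a simpler test and rests on assumed navigator numbers, caseloads and ICC, and the slope test adds a further unknown, the time course of any navigator effect. The consequence runs from negligible to material. This is a cheap improvement to the reporting of two key contrasts and does not invalidate the primary model.

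**What to change.** Leave the primary model unchanged and add the following.

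- State how many navigators there are, whether each participant keeps one, and whether the same navigators serve the PHN and PHN+SMS arms.
- Make sure a navigator ID is held for each participant in those two arms. The article does not say whether this is already done; data collection is expected to run to July 2027, so it can be secured while delivery is under way.
- Prespecify one sensitivity analysis beside the primary result. With enough navigators, use a partially nested GLMM with a navigator effect only in the PHN-containing arms and small-sample degrees of freedom. With too few to estimate a variance, report the contrasts over a range of assumed ICCs together with navigator-specific results, and limit the inference to those navigators.

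The cost is one administrative field and one extra analysis. The downside is that with few navigators the intervals will be wider and the variance component imprecise, which is why this belongs beside the primary result and not in place of it.

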## Methods

### Study Design

Following screening, informed consent, and baseline assessment, participants (N=195) are randomized (1:1:1) into: PHN alone (n=65), SMS text messaging alone (n=65), or combined PHN+SMS text messaging (n=65). The 3-arm repeated-measures design will assess participants at baseline, 3 (immediate effects), 6, 12 (sustained effects), and 18 (distal effects) months post randomization to determine the relative effectiveness of the interventions, including heterogeneous treatment effects across subgroups and over time, the implementation and sustainment costs of each intervention, and their cost-effectiveness relative to one another. The study uses an “intent-to-treat” design whereby all assessments are administered to all participants regardless of their level of participation or retention in the study (Figure 1).

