#### SMS Text Messaging

The SMS text messages are based on, and equally distributed across, three theories: social support theory (SST) [34-36], social cognitive theory [37,38], and health belief model (HBM) [39]. Table 1 illustrates how the SMS text message library was developed to have a theoretical foundation and be transculturally responsive. Participants receive three daily, theory-based SMS text messages for 90 days (270 unique scripted messages); participants do not receive the same scripted SMS text message twice. SMS text messages are evenly arrayed across: (1) HIV Care Continuum (HIV positivity/physical and emotional health, linkage/retention in HIV Care, and ART adherence/viral load suppression); and (2) theoretical foundation (SST, HBM, or SCT; Table 2).

SMS text messages are transmitted through gradual automation administration daily, including weekends, in real time, within a 10-hour period, and every 5 hours. Optimum hours were determined to be noon, 5 PM, and 10 PM, though participants may personalize the schedule to any 10-hour period and can choose to have the messages delivered through their cell phone or email. Both dosing (ie, three messages per day) and timeframe (ie, 10 hours) were determined during our prior SMS text messaging studies [23,25]. The intervention was designed to be cost-efficient, sustainable, and easily scaled by health clinics or community agencies. The automated SMS text message delivery system was developed by Dimagi [40]. Participants are asked to notify a research assistant immediately if they lose their cell phone or change their phone number or email address.

**Table 1 table1:** Sample Text Me, Girl! SMS text messages: displays theoretical foundation, HIV Care Continuum placement, and adaptation from a general message to a transspecific message.

Theoretical foundation	HIV Care Continuum	General message	Transspecific message
Social support theory	HIV positivity/physical and emotional health	Take care of yourself	Trans pride is taking care of yourself
Health belief model	Linkage/retention in HIV care	See your doctor	Protect your trans beautiful body, see your doctor
Social cognitive theory	ART^a^ medication adherence	Take your meds	Take your meds, girl! You can do it!

^a^ART: antiretroviral therapy.

**Table 2 table2:** SMS text message content by theoretical foundation.

			HIV Care Continuum							Total

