#### Power Analysis

A simulation approach was used to conduct the power analysis and determine that N=195 (65 per arm) was an appropriate sample size to detect the effect of each intervention on our primary outcome, and the likelihood of virologic suppression over time [67]. Power by simulation is more flexible than traditional approaches because it can estimate power under a wide variety of circumstances, including when these assumptions are not met.

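### Aim 1 tests arm differences in the slope of time although both interventions end at day 90: a held early advantage loses power, and a fading one can show a null or negative slope

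*Protocol article*

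**What the plan says.** The Protocol article, Statistical Analyses (Aim 1), sets the primary test: "Treatment condition will be used to predict the slope of time, creating a time × treatment interaction term that is the effect of interest". The same section describes this interaction as one "which will estimate the differential course and impact of the three intervention modalities over the follow-up period". Baseline belongs to the outcome series: "These outcome variables will be assessed at baseline and 3, 6, 12, and 18 months post enrollment". The primary outcome is binary viral suppression, below 200 copies/mL.

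The Study Design gives separate meanings to the visits: "baseline, 3 (immediate effects), 6, 12 (sustained effects), and 18 (distal effects) months post randomization". Delivery is short in both components. For navigation, "PHN sessions are unlimited for 90 days"; for messaging, "Participants receive three daily, theory-based SMS text messages for 90 days".

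The Power Analysis says that simulation showed 195 participants (65 per arm) to be an "appropriate sample size to detect the effect of each intervention on our primary outcome". It gives no effect size, trajectory, target power or significance level.

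**The concern.** All intervention contact falls in the first of six 3-month periods. A natural expectation is that arms separate by month 3 and then hold, narrow or converge. The Introduction also reports gains in the earlier projects as sustained through 18 months. A difference that appears by month 3 and holds is a step. One that appears and shrinks is a hump. A slope over 0 to 18 months fits neither well, and the immediate, sustained and distal effects cannot be read from it.

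With three arms the interaction has two degrees of freedom, so it is a pair of slope contrasts. Each contrast has the same weakness. At stake is the main conclusion of Aim 1: an arm with better suppression at follow-up could yield a null test, or a slope estimate pointing the other way.

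**Working it through.** **The plan's own figure.** Only 3 × 65 = 195 can be reproduced. For scale, a comparison of two proportions with 65 per arm, two-sided 5% and 80% power, detects 35% vs 59%, or 52% vs 75%.

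**Slope arithmetic.** Visits (Study Design): t = 0, 3, 6, 12, 18. Mean = 39/5 = 7.8. Deviations: −7.8, −4.8, −1.8, 4.2, 10.2. Sxx = 60.84 + 23.04 + 3.24 + 17.64 + 104.04 = 208.8. For a true between-arm difference x(t), the fitted change in the difference over 18 months is 18 × Σ(t − 7.8)x(t) / 208.8.

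- Held from month 3 (0, d, d, d, d): 18 × 7.8d/208.8 = +0.67d.
- Month 3 only: 18 × (−4.8d)/208.8 = −0.41d.
- Months 3 and 6: 18 × (−6.6d)/208.8 = −0.57d.
- Fading (d, 0.75d, 0.5d, 0.25d): 18 × (−1.5d)/208.8 = −0.13d.
- Fading by 24, 18, 8, 0 percentage points: −114/208.8 = −0.55 points per month, about −10 points over 18 months.

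**Other time codings.** The article does not state the metric, so the calculation was repeated over each scale's full range:

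| Shape | Months | Visit number | log(1 + month) |
|---|---|---|---|
| Held | +0.67d | +0.80d | +0.98d |
| Month 3 only | −0.41d | −0.40d | −0.21d |
| Months 3 and 6 | −0.57d | −0.40d | −0.11d |
| Fading to 0.25d | −0.13d | 0 | +0.25d |

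**Power for the held advantage.** With exchangeable correlation, efficiency relative to the best within-person contrast is [Σ(t − t̄)x]² / [Sxx × Σ(x − x̄)²]. In months this is 7.8² / (208.8 × 0.8) = 60.84/167.04 = 36%. A contrast with 80% power has expected z = 2.80. The slope then has 2.80 × √0.364 = 1.69, and power P(Z > 1.96 − 1.69) = 39%. Visit-number coding gives 50% efficiency and 51% power; log coding gives 73% and 67%.

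**Check on the binary scale.** A random-intercept logistic model was simulated for two arms of 65, with 400 trials per shape and baseline included. The reference course of 35% rising to 52% is the earlier messaging project's result (Introduction). The rest is assumed: log-odds advantage 1.5 (52% vs about 75%), random-intercept SD 1.8, 20% of follow-up visits missing at random, two-sided 5%.

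| Shape | Slope significant, right direction | Slope significant, wrong direction | Visit-based contrast |
|---|---|---|---|
| Held | 54% | 0% | 82% (post-baseline average) |
| Month 3 only | 0.3% | 9% | 62% (month 3) |
| Months 3 and 6 | 0% | 15% | 61% (month 3) |
| Fading to 0.25 | 1.5% | 1.5% | 61% (month 3), 45% (average) |
| Linear divergence | 72% | 0% | 36% (average) |

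For the held shape the slope had the right sign in 98% of trials. It was negative in 83% of month-3-only trials and 88% of months-3-and-6 trials. In the fading case the mean z was about 0.

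A three-arm version used 2-df tests, 1,000 trials, random-intercept SD 2.0 and 15% missed visits. One arm held 72% against 52% in the other two. Power was 41% for the slope interaction and 75% for a post-baseline contrast. When the better arm faded (76, 70, 60, 52%), the figures were 12% and 35%.

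**The case against.** **Shape.** The trajectory is not documented. Navigation works through linkage and self-efficacy, so arms could keep separating after day 90, and a slope does best if that divergence is linear. The article's own history is of sustained gains, the case in which the slope is weakened but correctly signed. This stands, and it is why the result is conditional on shape.

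**Coding.** The metric is unstated, and a SAP may settle it. That also stands. But the article positively names a slope, and the two alternative codings only reduce the loss. They do not change the sign for an advantage confined to month 3 or to months 3 and 6.

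**Other tests.** The plan also tests all other estimable effects and builds models iteratively. With time coded from 0, the arm main effect is the baseline difference, so it does not recover a follow-up effect. The iterative step adds explanatory factors and does not promise categorical or piecewise time.

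**Economic analysis.** It predicts means at each time period and reports 3 and 18 months separately. That gives immediate and distal comparisons on QALYs and HIV Care Continuum steps, but it is not the Aim 1 test of suppression.

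**Stronger readings to avoid.** A reader might infer that a sustained advantage would be mostly missed or reversed. A complete miss would require leaving baseline out of the outcome series, and Aim 1 lists it there. A reader might also infer that 195 participants are shown to be too few. The Power Analysis discloses no effect size, trajectory or target power, so nothing in the article can be refuted on that score.

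**Conclusion.** The concern holds in a limited form. The named effect of interest is poorly matched to 90-day interventions and to the three effects that the design distinguishes.

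With baseline included and time in months, a held advantage loses power without changing sign. An advantage confined to month 3, or to months 3 and 6, is almost never detected in the right direction and usually gets a negative slope. Significant results in the wrong direction are the minority in the simulation (9% and 15%). A gradual fade to a quarter of its size gives a slope near zero or slightly negative in months, zero with visit number and slightly positive with log coding.

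These sizes rest on the assumed trajectories, correlation and missingness; the direction of the slope arithmetic depends only on the visit times, the time coding and the shape. Whether the sample size was simulated for this slope test or for another contrast cannot be told from the article.

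**What to change.** In the Aim 1 model, treat time as categorical visit, or as piecewise linear with a knot at month 3. Name in advance, as the primary effect, the between-arm difference in viral suppression at one stated visit or averaged over the 3-18 month visits. Report the 3-, 12- and 18-month contrasts from the same model, so that the immediate, sustained and distal effects each have an estimate. Rerun the existing power simulation for the chosen contrast and state what difference 65 per arm detects. If categorical visits were intended all along, the slope wording should be replaced to say so.

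No visit or measurement changes. The cost is revised analysis wording, a rerun simulation and a few more parameters. The real trade-off is efficiency if arms diverge linearly over 18 months: in the two-arm simulation the slope then had 72% power against 36% for the post-baseline average. The change should be made before outcome data are compared by arm; data collection is expected to run to July 2027.

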### Randomization

Stratified block randomization with random block sizes is used to assign participants to each of the 3 study arms. To ensure balance with respect to certain covariates, participants are grouped by three stratification factors: (1) age (<35 and ≥35 years), (2) race or ethnicities (Latinx, all other race or ethnicities), and (3) HIV Care Continuum placement (linked, not linked to HIV care). Block randomization helps ensure balance in the number of participants assigned to each arm, while random block sizes make the sequence of assignments less predictable to research staff.

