#### HIV Health Assessment

The assessment records demographics (eg, sexual identity, age, and race or ethnicity), educational attainment, housing status, access to insurance, HIV treatment status (including the position in the HIV Care Continuum), HIV medication status (including medication type and dose), and self-reported ART adherence.

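### Linkage to HIV care is a randomisation stratum, but the Aim 1 model does not secure it, because further factors enter by likelihood-ratio test

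*Protocol article*

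**What the plan says.** The Randomization section of the protocol article describes the allocation: "Stratified block randomization with random block sizes is used to assign participants to each of the 3 study arms". The first two stratification factors are "1) age (<35 and ≥35 years), (2) race or ethnicities (Latinx, all other race or ethnicities"). The third is "HIV Care Continuum placement (linked, not linked to HIV care").

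Under Statistical Analyses, Aim 1, each outcome is regressed on treatment condition, "a set of baseline covariates (individual-level demographic characteristics), and time-varying covariates (social and structural determinants of health"). The effect of interest is the time × treatment interaction, estimated over baseline and months 3, 6, 12 and 18 in a generalized linear mixed model.

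The same section then gives a model-building rule. The simplest model is fitted first, and explanatory factors are added step by step, with those that theory ranks highest going in first. The admission test is stated as follows: "Likelihood ratio tests are used to determine if the more complicated of the 2 models is a significant improvement over the simpler model". A further sentence keeps variables of interest, such as those specified in Aim 1, in the final model whatever their significance.

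**The concern.** When allocation is balanced within strata, the usual practice is to carry the stratification factors into the primary model whatever their significance. Here one of the three has no assured place. Two things could be at stake.

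- **Prespecification.** A logistic odds ratio is conditional on the covariates in the model. If tests on the outcome data choose those covariates, the primary quantity is not fully defined before the data are seen.
- **Precision.** If allocation is balanced on a prognostic factor and the analysis ignores it, the model-based standard error of an arm contrast is too wide and the test is conservative.

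The article itself gives reason to think linkage matters. Its Background treats linkage and retention as critical to suppression, and linkage is one of only three factors chosen for balance.

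**Working it through.** **1. Is each stratification factor in a named covariate set?**

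| Stratification factor | Demographic baseline set | Social and structural set |
|---|---|---|
| Age group | yes | no |
| Race or ethnicity | yes | no |
| Linked / not linked | no | no |

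The HIV Health Assessment section shows how the article uses the word demographics: "The assessment records demographics (eg, sexual identity, age, and race or ethnicity"). It lists position in the HIV Care Continuum separately, under HIV treatment status. The Primary and Secondary Aims section gives examples of social and structural determinants (poverty, housing, food, education, insurance), and linkage is not among them. Linkage could therefore enter only as an added explanatory factor that passes a likelihood-ratio test.

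**2. The plan's own figure.** No stated figure turns on this point. N=195 is 3 × 65. The power simulation behind it cannot be rerun, because the article gives no suppression rates, significance level, correlation or dropout. All inputs below are assumptions: 50% mean suppression, strata of 99 and 96, balance within stratum, and a 5% likelihood-ratio test.

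**3. Arm contrast at a single time point** (logistic regression, N=195, 4,000 runs; power at a conditional odds ratio of 2.5).

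| Gap in suppression, linked vs not | Test admits linkage (null runs) | Type I error, omitted / included | Power, omitted / included |
|---|---|---|---|
| 5 points | 10% | 0.042 / 0.043 | 0.699 / 0.703 |
| 10 points | 29% | 0.038 / 0.042 | 0.713 / 0.722 |
| 15 points | 56% | 0.043 / 0.050 | 0.696 / 0.712 |
| 20 points | 80% | 0.045 / 0.052 | 0.687 / 0.707 |
| 30 points | 99% | 0.033 / 0.053 | 0.646 / 0.681 |
| 40 points | 100% | 0.029 / 0.050 | 0.574 / 0.642 |

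A hand calculation for the 30-point gap (65% vs 35%, equal strata) agrees in direction:
- R² = 0.15² / 0.25 = 0.09.
- Standard error ratio = 1/√(1 − 0.09) = 1.048.
- Type I error = 2 × [1 − Φ(1.96 × 1.048)] = 0.040.

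The fitted odds ratio also depends on whether linkage is in the model. At the 40-point gap it averages 2.19 with linkage omitted and 2.55 with it included.

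**4. The planned time × treatment term** (random-intercept logistic model, five visits, random-intercept SD 1.5, true slope difference 1.4, 300 runs).

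| Log odds ratio for linkage | Estimate, omitted / included | Standard error, omitted / included | Power, omitted / included |
|---|---|---|---|
| 0.5 | 1.444 / 1.444 | 0.558 / 0.558 | 0.740 / 0.740 |
| 1.5 | 1.391 / 1.392 | 0.570 / 0.570 | 0.683 / 0.687 |
| 3.0 | 1.335 / 1.337 | 0.621 / 0.618 | 0.563 / 0.570 |

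The random intercept absorbs a fixed baseline factor, so the interaction hardly changes. The test admits linkage in 47% of these trials at log odds ratio 0.5 and in all of them at 1.5 and 3.0.

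**5. Does selection by test itself do damage?** In the single-time-point setting, letting the test decide was compared with always including linkage (4,000 runs). Type I error was 0.044 and 0.044 at a 10-point gap, 0.049 and 0.049 at 20, and 0.054 and 0.054 at 30. Power was 0.722 and 0.723, 0.700 and 0.700, and 0.666 and 0.666. A rerun with a different seed gave the same pattern.

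**The case against.** The strongest reply is that the mechanism and the harm hardly ever occur together. A factor strong enough to matter nearly always passes the likelihood-ratio test, and one weak enough to fail it costs almost nothing when left out. Steps 3 and 5 bear this out. The loss in step 3 needs a strongly prognostic linkage factor that is never offered as a candidate, and the article does not say that will happen. This stands, and it removes most of the precision argument.

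A second reply is that a condensed article may leave the list of stratification factors to the analysis plan, and that its mention of demographics is only a summary. This stands in part. The text does not forbid linkage, and a fuller plan may include it. But the article is not merely silent: it states a covariate set and a data-driven admission rule, and together they leave a stratification factor unsecured.

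Three stronger readings are tempting and are not supported:

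- **Age and ethnicity could also be dropped.** The retention clause points to variables specified in Aim 1, and the demographic covariates are named under that heading. They are plausibly protected.
- **The primary test loses power or is too conservative.** The stated effect of interest is the interaction, for which step 4 shows practically no change.
- **Selection inflates the type I error.** Step 5 shows no inflation from selecting on this factor. Selection over the wider covariate set was not examined.

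**Conclusion.** The point holds as a matter of prespecification and of consistency between design and analysis. Two of the three stratification factors fall in the named baseline set. Linkage falls in none, and the stated rule lets the outcome data decide on it. At assumed gaps of 5 to 15 points in the single-time-point setting, a 5% test would leave linkage out in roughly 45% to 90% of trials, so its inclusion is genuinely open.

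The numerical consequence for the planned time × treatment term is about nil: power differs by less than 1 percentage point even at a log odds ratio of 3.0. For an arm contrast at one time point, leaving linkage out costs 0 to 7 points of power and can bring the type I error down to about 0.03, with the larger losses at gaps of 30 to 40 points. The prognostic gap, suppression rates, random-intercept SD and test level are all assumptions, since the article gives none of them for this trial. This is an inexpensive improvement and not a threat to the validity of the primary test.

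**What to change.** State under Statistical Analyses, Aim 1 that the three stratification factors, as used at randomisation, are always included in the primary model regardless of significance. Confine the iterative likelihood-ratio model building to secondary explanatory models.

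Do not add baseline viral suppression as a further covariate while baseline is one of the modelled repeated responses. That would put the same measurement on both sides of the model unless the model were restructured.

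The cost is wording only. Stratum values exist for every participant at randomisation, no new data are needed, and the primary analyses start only after follow-up ends, with data collection expected to finish in July 2027.
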